### Statistical analysis

Quantitative data is analyzed by descriptive statistics for demographic, socio-economic and other patient-, provider- and health system level factors between the intervention and control facilities. Differences in service delivery indicators, process of care measures (prescription of guideline directed medical therapy) and clinical outcomes (BP control) will be compared between the intervention and control facilities. The chi-square test is used to evaluate differences between categorical variables. Two-sided p-values < 0.05 will be considered statistically significant. Composite performance scores are defined by determining the proportion of patients who receive concordant care compared to patients who receive discordant care between the intervention and control facilities. Linear and logistic regression analysis techniques are used to assess determinants of health outcomes, processes of care measures, and treatment satisfaction [33]. Random-effects regression analyses will be used to account for cluster effects and imbalances between intervention and control group health facilities; Effect sizes will be presented as risk ratios for binary outcomes, and as mean differences for continuous outcomes; 95% confidence intervals (CI) will be given for both. Missing data in outcome measures will be handled by appropriate imputation methods.

A propensity score will also be created using logistic regression and will contain those variables associated with treatment at a health facility [34]. Analysis of clinical outcomes analysis will also use ANCOVA (analysis of covariance) to compare the prescription of evidence-based medicines, and mean change in BP and lipids between the intervention and control arm facilities [29]. Other outcome measures such as behavioural and biochemical risk factors will be analyzed using logistic or conditional logistic regression to adjust the comparisons for other variables. We shall also compare the percentages achieving clinical and behavioural targets between the intervention and control arm facilities.

The fidelity analysis will uncover the extent to which the GHI was fully or partially implemented by various health system stakeholders.

Next, when analyzing the KAP survey we will report the demographic characteristics of healthcare providers by the intervention and control arm facilities, reporting the mean (standard deviations, SD) or median (25th and 75th percentiles) for continuous variables and frequencies (percentages) for categorical variables. Knowledge about CVD symptoms and modifiable risk factors will be reported as number (percent) by overall and intervention and control arm facilities. Next, each correct response for knowledge related questions will be assigned a score of 1 and the total score for the knowledge of CVD risk factors and treatment recommendations will divided by tertiles and classified as minimal, moderate, and high knowledge. The mean (SD) for knowledge of CVD risk factors and treatment will also be reported by intervention and control facilities. Finally, the correct scores for the knowledge of CVD risk factors and treatment strategies will be classified into high knowledge (> 75% correct responses) and poor knowledge (≤ 75% correct responses) using arbitrary threshold for comparison and also informed by the published literature [35] [36]. The chi-square test will be performed to investigate the difference in knowledge scores between intervention and control arm facilities across age-group, sex, and education strata. Bivariable and multivariable regression analyses will be performed to assess the factors associated with high knowledge of CVD symptoms, and modifiable risk factors. The unadjusted and adjusted odds ratio with 95% confidence intervals (CI) will be reported. The model will be adjusted for age, sex, type of health facility and type of healthcare worker.

Lastly, an interrupted time-series analyses (ITSA) is carried out to establish effects of the GHI on the screening, diagnosis, and management of hypertension / CVD, if aggregate facility-level monthly data are available from the DHIMS2. ITSAs apply segmented regression to assess the impact of events that have occurred at a clearly defined point in time. Data points recorded in the GHI enabled DHIMS2 system will be analyzed by month to examine trends over time and seasonality. We will also evaluate change in patient outcomes over time (e.g., mean systolic BP change).

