**Methods::**

This study adopts a mixed- and multi-methods design comparing the effects of the GHI in 42 intervention health facilities (i.e. primary, secondary and tertiary) in the Greater Accra Region versus 56 control health facilities in the Central and Western Regions. The evaluation design is guided by the RE-AIM framework underpinned by the WHO health systems building blocks framework, integrated by the Institute of Medicine’s six dimensions of health care quality: safe, effective, patient-centered, timely, effi cient, equitable. The assessment tools include: (i) a health facility survey, (ii) a healthcare provider survey assessing the knowledge, attitudes, and practices on hypertension and CVD management, (iii) a patient exit survey, (iv) an outpatient and in-patient medical record review and (v) qualitative interviews with patients and various health system stakeholders to understand the barriers and facilitators around the implementation of the GHI. In addition to primary data collection, the study also relies on secondary routine health system data, i.e., the District Health Information Management System to conduct an interrupted time series analysis using monthly counts for relevant hypertension and CVD specific indicators as outcomes. The primary outcome measures are performance of health service delivery indicators, input, process and outcome of care indicators (including screening of hypertension, newly diagnosed hypertension, prescription of guideline directed medical therapy, and satisfaction with service received and acceptability) between the intervention and control facilities. Lastly, an economic evaluation and budget impact analysis is planned to inform the nationwide scale-up of the GHI.

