## Methods

### Study Setting

Ghana is a lower-middle-income country with an average annual per-capita gross domestic product of US$2,445.3 [18]. The mortality from coronary heart disease in 2020 was 119.93 per 100.000 population, and the probability of dying from any of CVD, cancer, diabetes and chronic respiratory disease is 20.8% [19]. The health system in Ghana is decentralized, pluralistic, and operates on an integrated three-tier (national, regional, and district) scheme and incorporates a community-level health delivery system to support community-based primary healthcare [20]. Most healthcare is provided by the government and is largely administered by the service delivery agencies under the MoH such as the Ghana Health Service (GHS), teaching hospitals, and the private providers (self-financing, faith-based, and non-governmental organisations). Ghana reformed its National Health Insurance Scheme in 2003 with 40% of the population being enrolled and ~ 60% enrolled people are exempted from premium payments [21]. Ghana is one of the first African nations to enact legislation and earmark financing for universal health coverage; a significant move towards health system strengthening and improved financial protection [21].

Accra is the capital city of Ghana and is located in GAR, which is one of the 16 administrative regions, and has the highest population density. The GAR has 26 districts, including the Accra Metropolitan Assembly, and had a total population of 5.4 million in 2021. The pilot phase of the GHI was implemented in 42 health facilities located in five districts (Accra Metro, Tema Municipal, Ga East, Ga West, Dangme West and Dangme East). A health facility is an infrastructure built and licensed by the Health Facilities Regulatory Authority to take care of the healthcare needs of the citizens of Ghana.

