The comprehensive evaluation is being conducted in those 42 health facilities implementing GHI with matched control health facilities. Matching of intervention and control facilities was done based on pre-determined variables such as the level of care (primary, secondary, or tertiary), volume of outpatient visits, bed capacity and availability of human resources (number of physicians, nurses, and other allied healthcare professionals). The data on the facility level characteristics was obtained from the GHS and the Christian Health Association of Ghana (CHAG) Secretariat (the largest faith-based health service provider in Ghana) and we considered a large pool of potential ‘control’ health facilities from the Central Region and Western Region (Fig. 1). The advantage of using a quasi-experimental design with matched control facilities ensures that all the exposure variables stay the same across the intervention and control facilities except for the intervention arm, i.e., GHI-related activities.

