### Conceptual framework

In line with the abovementioned implementation science approach and the aforementioned research questions, our study adopts the RE-AIM framework as the guiding operational evaluation framework. The RE-AIM framework offers a comprehensive structure that will guide the quantitative and qualitative data collection to systematically evaluate the robustness of the intervention (“the GHI”) across the RE-AIM domains – reach, effectiveness, adoption, implementation, and maintenance as well as related costs, and the potential for scaling up the intervention to other regions in Ghana [22]. It should be noted, that within the effectiveness domain, some of the indicators may have elements to estimate impact, where we hope to carry out a Difference-in-Difference (DID) analysis and if routine health data is available an interrupted time series-analysis (ITSA) enabling a quasi-experiment to attribute causality to the intervention.

The Theory of Change (ToC) development was informed by a discussion with stakeholders of how the intervention (“the GHI”) induced changes in the management of hypertension and CVD care in a “real-world setting”, a description of the health systems pathway through which this change was expected to happen, and the RE-AIM evaluation framework to assess whether and how change has happened [23] [24].

Considering the content of our intervention specifically, we turned to the World Health Organization’s (WHO) six health system building blocks (HSBB) to structure our work [25]. We did so out of a desire to analyze systematically how the actions carried out by the GHI had produced effects on each of the six HSBB. The WHO HSBB at health facilities enables a comprehensive evaluation of the health system performance, clinical, processes of care and quality of care outcomes. Further, understanding implementation outcomes (fidelity, acceptability, and effectiveness) of the intervention using a conceptual ToC model from diverse user’s perspectives can support consideration of how and why the intervention is likely to generate the changes observed and assist in thinking through the potential for the expansion and scale-up of the GHI in contextually similar settings. It may also contribute to consideration of how to manage implementation over time and highlight factors that are likely to support the sustainability and achievement of long-term goals of the GHI.

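### Arm and region coincide, so the planned 95% CIs and p-values cannot separate a GHI effect from a regional difference and overstate certainty whenever regions differ

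*Protocol article*

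**What the plan says.** The abstract (Methods) compares "42 intervention health facilities (i.e. primary, secondary and tertiary) in the Greater Accra Region" with "56 control health facilities in the Central and Western Regions". Under Study Setting, the article adds: "The pilot phase of the GHI was implemented in 42 health facilities located in five districts". No region contains facilities of both arms.

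Controls were matched on "level of care (primary, secondary, or tertiary), volume of outpatient visits, bed capacity and availability of human resources". Study Setting then claims that the matched quasi-experimental design "ensures that all the exposure variables stay the same across the intervention and control facilities except for the intervention arm".

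Under Statistical analysis: "Random-effects regression analyses will be used to account for cluster effects". The sentence goes on to imbalances between intervention and control health facilities. Facility is the natural reading of the cluster level, although the level is not named. Effects are to carry 95% CIs, and two-sided p < 0.05 counts as significant. Plain chi-square tests are also planned. Region appears neither in this section nor in the limitations, where the remedy for imbalance is adjustment for patient or provider characteristics.

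Under Conceptual framework, difference-in-difference and interrupted time-series analyses are described as "enabling a quasi-experiment to attribute causality to the intervention". The first is only hoped for, on some indicators, and the second depends on routine data being available.

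**The concern.** Whatever is common to all facilities of a region (case mix, urbanisation, staffing supply, reporting habits, regional programmes) is also common to a whole arm or to half of the control arm. The article itself notes that Greater Accra contains the capital and has the highest population density. For this source of variation the comparison is one region against two, not 42 facilities against 56.

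Facility-level clustering treats the 98 facilities as separate evidence on the arm difference. That is right for facility variation and wrong for anything shared within a region. Matching on four facility traits and adjusting for patient or provider traits do not break the overlap either.

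Two things follow. The point estimate mixes GHI with region, which is confounding. The interval around it, if read as uncertainty about GHI, is too narrow, and more records or more facilities in the same regions do not change that. The results are meant to inform national scale-up, so a regional difference reported as a significant GHI effect would matter.

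**Working it through.** **Inputs from the article.** 42 facilities in 1 region; 56 facilities in 2 regions; 1,200 participants less 20% non-response = 960 evaluable; two-sided 0.05; 95% CI. The 1,200 itself cannot be reproduced, because no baseline rate is stated. It is used here only as a volume of data, and the point does not depend on it.

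**Assumptions, none of them in the article.** A binary outcome at 50%; facility ICC 0.05; equal numbers per facility; controls split 28 and 28; regional SD tau varied.

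**Facility-only standard error, one wave.** Per facility 960/98 = 9.8, so n = 411 and 549. Design effect = 1 + 8.8 x 0.05 = 1.44. SE = sqrt(0.25 x 1.44 x (1/411 + 1/549)) = 3.91 points.

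**Facility-only standard error, two waves.** Per wave 480 records, 4.9 per facility, n = 206 and 274. Design effect = 1 + 3.9 x 0.05 = 1.195. SE of the difference in change = sqrt(2 x 0.25 x 1.195 x (1/206 + 1/274)) = 7.13 points, treating facility effects as independent between waves. If they persist, this SE is smaller and the inflation below is larger.

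**Adding region.** One treated region against the mean of two control regions adds tau^2 x (1/1 + 1/2) = 1.5 tau^2 to the variance. An uneven control split raises the factor (42 and 14 gives 1 + 0.75^2 + 0.25^2 = 1.625).

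Full SE = sqrt(SE_facility^2 + 1.5 tau^2). False-positive rate of the nominal 5% test = 2 x (1 - Phi(1.96 x SE_facility / full SE)).

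| Regional SD (points) | One wave: full SE | One wave: false positives | Two waves: full SE | Two waves: false positives |
|---|---|---|---|---|
| 0 | 3.91 | 5.0% | 7.13 | 5.0% |
| 1 | 4.10 | 6.1% | 7.23 | 5.3% |
| 2 | 4.62 | 9.7% | 7.54 | 6.4% |
| 4 | 6.27 | 22% | 8.65 | 11% |
| 6 | 8.33 | 36% | 10.24 | 17% |

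In the one-wave columns tau is the SD of regional levels. In the two-wave columns it is the SD of regional changes. These are different quantities, and the same values are used only for display.

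**Check by simulation.** Facility-level t-tests with 12 patients per facility, facility ICC 0.05 and no GHI effect gave 11.4%, 19.9%, 30.3% and 43.8% false positives at regional variance shares of 0.002, 0.005, 0.01 and 0.02. The formula gives 11.7%, 20.7%, 31.7% and 44.9% for 1,200 patients.

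**Floor.** The term 1.5 tau^2 does not shrink with sample size. A regional SD of 3 points alone gives an SE of 3 x sqrt(1.5) = 3.7 points.

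**Could a region random effect repair it?** One treated and two control regions leave 1 degree of freedom, with a t critical value of 12.7. The regional variance cannot usefully be estimated from these data.

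**The case against.** The best case against has four parts.

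- *The article does not state what is being criticised.* It speaks of cluster effects without naming the level, and it does not say that the two control regions will be merged. Random-effect levels and region terms are often left to an analysis plan that is not shown. This stands in part: a reader might infer that the plan specifies a facility-only model that pools Central and Western, and the text does not go that far. But no choice of level removes the overlap of arm and region, and the matching assurance under Study Setting is a positive claim, not a missing detail.
- *This is confounding, not a miscomputed standard error.* With three named regions held fixed, a facility-clustered interval is valid for the difference between these regions. That is correct. A reader might infer that the regression is computed wrongly, and it need not be. The error lies in reading that interval as uncertainty about GHI. The false-positive rates above apply when regions are regarded as varying around a common level.
- *It is partly handled.* The record review covers both arms before and after GHI, and DHIMS2 offers monthly series. Contrasts of change remove time-constant regional differences. They do not remove region-specific change, they are hoped for or conditional, and the provider and exit surveys (provider knowledge, patient satisfaction) have no stated baseline.
- *The size is assumed.* This stands in full. At a regional SD of 1 point the inflation is slight. A reader might take the 36% row as the expected error rate, but nothing in the article supports choosing that row.

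**Conclusion.** The point holds in this form. Arm and region coincide, and neither the planned clustering nor the planned adjustment can tell a GHI effect from a regional difference or a region-specific change. The stated CIs and p-values describe patient and facility sampling within three regions. As statements about GHI they are too certain whenever regions differ.

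The direction is certain if regional variance exceeds zero. The size is unknown. For SDs of 1 to 4 points the illustration runs from about 6% to 22% false positives with one wave and 5% to 11% with two, under an assumed ICC of 0.05, a 50% outcome and an even control split. The inflation is greatest for outcomes without a baseline.

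The sentence that is wrong as it stands is the claim that matching keeps everything but GHI the same. Four matched facility characteristics cannot ensure that across regions.

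**What to change.** 1. Beside the pooled arm contrast, report Greater Accra versus Central, Greater Accra versus Western, and Central versus Western. The last is a descriptive gauge of how far two regions differ without GHI.
2. State that CIs and p-values are conditional on these three regions, and show them widened over a range of assumed regional SDs. With the inputs above, the one-wave half-width of 7.7 points becomes 8.0, 9.0 and 12.3 at SDs of 1, 2 and 4.
3. Where before/after data exist (record review, DHIMS2), base the effect claim on the difference-in-difference or controlled time-series contrast, and say that region-specific change remains.
4. Withdraw the matching assurance under Study Setting and name region as a confounder in the limitations.

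Do not turn the Central versus Western contrast into a pass/fail test. A rule that both Greater Accra contrasts agree in direction and exceed it is met about 30% of the time with no GHI effect. Combined with p < 0.05 it still gives about 7%, 14% and 20% false positives at regional SDs of 2, 4 and 6 (simulated with the one-wave inputs). A district random intercept is not a remedy either, because it does not capture variation shared by a whole region.

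Cost: wording, a few more rows per table and one sensitivity display, with no new data. Some results will be stated less firmly.

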The medical records of outpatient and inpatient folders at two cross-sectional timepoints before and after GHI implementation are being reviewed to assess between group differences in hypertension and CVD care delivery. Eligibility of medical records are pre-specified based on confirmed diagnosis of hypertension or CVD, and complete medical records with at least data available on patient demographics (age, sex), medical history (confirmed case of hypertension or CVD), laboratory results (any test prescribed, or test reports reviewed), and medical treatment or prescription.

Lastly, DHIMS2 data routinely collected by the MoH in Ghana to monitor service provision consisting of monthly facility-specific counts for a wide range of services, including CVD will be analyzed to assess the differences in care delivery between the intervention and control health facilities over the time period. In line with prior work, to translate monthly counts into indicators that adequately capture service coverage, we construct outcome variables that account for the underlying target population living in the catchment area of a given facility [32]. More specifically, we apply interrupted time series analysis to DHIMS2 data to assess impact on the following CVD indicators: prevalence of hypertension, coronary heart disease, stroke, heart failure and related mortality.

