### Sample size

The sample size of 1,200 participants in total for the MRR or patient exit survey will provide 90% power to detect 10% relative difference between the intervention and control facilities in processes of care indicators such as prescription of evidence-based therapies and blood pressure control. at an α = 0.05 and accounting for 20% non-response rate or missing data.

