### Evaluation Design Strengths and Weaknesses

The mixed-methods triangulation study is the first of its kind for LMICs and in sub-Saharan Africa, testing a comprehensive and multifaceted health system intervention addressing hypertension and CVD management. The evaluation is rigorously designed, factoring in multiple data sources, minimizing biases using matched control health facilities, data triangulation using quantitative survey and qualitative interview data, and economic evaluation. The ToC was developed in a participatory manner in collaboration with GHI programme implementers helping the evaluators to understand where the intervention tried to produce a change and led to a commonly defined TOC and definition of indicators. Our focus is centered more on a theory-driven evaluation and the fact that we will work “closer to reality” but far from a real experiment or quasi-experiment. To avoid contamination between the intervention and control facilities, the data collection for control group facilities and participants will be accomplished by a separate team of trained field enumerators. However, in a real-world setting we cannot avoid spillover of intervention components to other regions since the national guidelines for the management of CVD were signed by the Minister of Health in 2021 and offi cially launched in August 2022 by the MoH and is available in the public domain and can be accessed via the AkomaCare App (https://akomacare.org/download) [47]. The data collection timepoints for the MRR before and after GHI implementation has been prespecified in both the intervention and control health facilities to avoid any seasonal variations in the hypertension and CVD care outcomes. Furthermore, we customized the survey questionnaires developed with an open-source platform called Survey Solutions (https://mysurvey.solutions/en/) developed by the World Bank. Data is entered on Android-based tablets using the Survey Solutions Interviewer App, stored locally on the tablets, and synchronized regularly to HIGH’s virtual server, enabling real time tracking and remote data monitoring. The Survey Solutions Designer allows the inclusion of instructions visible in blue for each question as the interviewer progresses through the survey. This digital data collection approach along with its technical features improves data quality and reduces data entry errors or missing values.

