**Figure 4 F4:**
[figure not shown]
Summary of the evaluation components, tools and outcomes measures *Fidelity and Acceptability were only assessed in the interventional health facilities. KAP = Knowledge, attitude and practice.

**Table 1 T1:** Health service delivery evaluation: domains, indicators, and tools.

Domains	Process Indicators	Outcome Indicators	Sustainability Indicators
Safety	No. and proportion of sites having access to guidelines, equipment; Type of out-patient and emergency services available by facilities.	Annual death rate for CVD; Incidence of CVD; Prevalence of hypertension; Prevalence of CVD	Workforce appropriate (workforce adequate in volume and distribution); Equipment adequate.
Tools	Health facility survey; Key informant Interviews	Health facility survey; DHIMS2 dataset	Health facility survey; Key informant Interviews
Timeliness	Annual hypertension screening coverage; CVD preventive and treatment services offered.	Total waiting time for physician consultations; Total in-person consultation time; Treatment received within 24 hours of CVD admission.	Workforce sustainability (staff retention per year, staff stability per year).
Tools	Health faclity survey	Health facility survey	Key informant interviews
Effectiveness	No. of HTN patients seen; No. of CHD patients seen; No. of stroke patients seen; No. of heart failure patients seen; No. of hospitalizations by CVD conditions; Average length of hospital stays (in days); No. of acute emergency transfers related to CVD; No. of referrals to higher facilities for CVD; No. of referrals to lower health facilities for CVD.	No. and proportion of patient diagnosed with hypertension; Number and proportion of patients diagnosed with CVD; Number and proportion of CVD patients prescribed evidence-based medicines; Number and proportion of patients with BP < 140/90; Number and proportion of patients with LDLc< 100 and < 70 in those with CVD; Number and proportion of patients who do not smoke.	Linkages - referral pathways (coordination of care across providers, specialist access); No of referrals per year; No of specialist consultations per year.
Tools	Health facility survey	Health facility survey; DHIMS2 dataset; Patient exit survey	Health faclity survey; Key informant interviews
Patient centered care	No. of follow-up appointments.	Treatment satisfaction; Proportion of patients in regular follow-up.	Infrastructure (IT-internet access, equipment access, staff availability or shortage)

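### No arm-by-period model is stated for the unlinked before-and-after medical records; the named ANCOVA on mean change does not fit that sampling

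*Protocol article*

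**What the plan says.** Under Data collection Tools, Indicators, and Strategies the article states: "The medical records of outpatient and inpatient folders at two cross-sectional timepoints before and after GHI implementation are being reviewed". The purpose given is to assess differences between the groups. Nothing says that the same patients are found again at the second time point.

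Under Statistical analysis, clinical outcomes are to be analysed by "ANCOVA (analysis of covariance) to compare the prescription of evidence-based medicines, and mean change in BP and lipids". The other methods there are chi-square tests, composite scores, linear and logistic regression, random-effects regression and a propensity score. Where a contrast is given, it is intervention against control facilities. No time point, period term or arm-by-period term is stated.

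DID appears once, under Conceptual framework, for some effectiveness indicators: "where we hope to carry out a Difference-in-Difference (DID) analysis". An interrupted time series is planned if facility-level monthly routine data are available.

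The Sample size section gives one figure, "The sample size of 1,200 participants in total for the MRR or patient exit survey", with 90% power for a 10% relative difference between intervention and control facilities, "at an α = 0.05 and accounting for 20% non-response rate or missing data".

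**The concern.** ANCOVA on change needs a baseline and a follow-up value on the same unit. Two unlinked cross-sections of records do not give that for patients. Prescription is a yes/no outcome, for which the same section promises risk ratios, and ANCOVA does not produce these.

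The larger issue is identification. All 42 intervention facilities are in the Greater Accra Region and all 56 controls are in the Central and Western Regions. Any fixed difference between the capital region and the other two in prescribing or BP control is confounded with the initiative. The before-period records are the patient-level data that could separate the two, and the stated analysis gives them no explicit place in an effect estimate. Prescription and BP control are both listed as primary outcomes.

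**Working it through.** **Step 1. Sampling against method.**

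| Element | Stated in the article | Consequence |
|---|---|---|
| Record review | Two cross-sectional time points, no linkage described | No patient-level change as described |
| ANCOVA | Prescription; mean change in BP and lipids | Wrong outcome type for prescription; no patient baseline for change |
| Chi-square, regression, random-effects models | Arm contrast, no period term stated | Before-period has no stated role in the estimate |
| DID | Hoped for, some indicators | Fits the sampling but is not committed to |
| Interrupted time series | If routine data are available; the Data collection section lists disease prevalence and mortality | Does not clearly cover prescription or BP control |

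**Step 2. What the 90% power refers to.** Inputs from the article: two-sided α 0.05 ("Two-sided p-values < 0.05 will be considered statistically significant"), power 90%, total 1,200, 20% loss. Evaluable: 1,200 × 0.8 = 960, or 480 per arm if split equally (assumed). The control rate is not given, so 1,200 cannot be strictly reproduced. With the pooled-variance formula

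n per arm = [1.96√(2p̄(1−p̄)) + 1.2816√(p(1−p)+q(1−q))]² / (q−p)², total = 2n/0.8,

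- a 10% relative difference (q = 1.1p) needs 5,238 at a 50% control rate, 2,085 at 70%, 1,560 at 75% and 1,100 at 80%;
- a 10-point absolute difference, 30% vs 40% or 60% vs 70%, needs 1,193.

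On either reading the figure is a two-group contrast at one time, not a difference in change.

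**Step 3. Illustration of a fixed regional gap.** Assume no effect, one time point, 480 per arm, an unadjusted two-proportion test and no clustering. The test rejects with probability

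Φ{ [d√480 − 1.96√(2p̄(1−p̄))] / √(p(1−p)+q(1−q)) }, where d = q − p.

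- 50% vs 55%: 0.34
- 50% vs 60%: 0.88

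If 1,200 covers both periods (240 per arm after), these fall to 0.19 and 0.60. With 480 per arm, an assumed intracluster correlation of 0.05 and about 10 patients per facility (960/98), the design effect is 1 + 9 × 0.05 = 1.45. A test that allows for it gives 0.25 and 0.74. The documents give neither the gaps nor the rates.

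**Step 4. Power of the DID.** Four independent cells of n, three at rate p and one at q = 1.1p, no clustering:

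SE = √{[3p(1−p) + q(1−q)]/n}, power = Φ{(q−p)/SE − 1.96}.

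Example, p = 0.50, q = 0.55, n = 240: SE = √[(0.75 + 0.2475)/240] = 0.0645; 0.05/0.0645 = 0.776; power = Φ(−1.184) = 0.12.

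| Assumed control rate | 1,200 over both periods (240 per cell) | 1,200 per period (480 per cell) |
|---|---|---|
| 50% | 12% | 19% |
| 60% | 16% | 27% |
| 70% | 23% | 40% |
| 80% | 37% | 63% |

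**Step 5. Width.** At 50% vs 55%, a one-time contrast with 480 per arm has SE √[(0.25 + 0.2475)/480] = 0.032. The DID has 0.046 (480 per cell, about 1.4 times) or 0.064 (240 per cell, about twice).

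**The case against.** The strongest reply is that the plan is underspecified, not wrong. Much of it stands, and it limits the point.

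- A reader might infer that the comparisons use after-period data only. The text does not say so: Statistical analysis gives no time point, and the random-effects regression could carry an arm-by-period term. None is stated.
- A reader might infer that ANCOVA is impossible here. It is not. Facilities recur, so the after-period facility mean can be adjusted for the before-period mean. Records from 2018 to 2022 may also hold repeated BP values. The article neither states nor excludes either.
- A reader might infer that the before-data are never used. The article does plan a conditional interrupted time series, described in Statistical analysis as covering management, and an evaluation of systolic BP change over time. The time series uses monthly aggregate counts, and the BP evaluation has no stated comparator model.
- Facilities are matched on level of care, volume, beds and staffing, and a propensity score and adjusted analyses are planned. A regional gap therefore need not pass through in full. These measures do not remove an unmeasured regional difference, because no region contains both arms.
- Table 1 lists "Health facility survey; DHIMS2 dataset; Patient exit survey" as the tools for prescription and BP below 140/90 and does not name the record review. This does not show that record data are excluded, since the facility survey is described as including clinical records.

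An unseen analysis plan may supply model detail. It would not cure a named method that does not fit the sampling described.

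**Conclusion.** The point holds in this limited form. Patient-level mean change by ANCOVA is unsupported by the record sampling as described, ANCOVA is named for a binary outcome, and no stated patient-level model uses the before-period to separate initiative from region for prescription or BP control.

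The size of any bias cannot be read from the documents. The 34% and 88% figures show how sensitive a one-time contrast would be under the assumptions in the working; they are not the error rate of this plan. The power result is firmer in direction: the 90% belongs to a two-group contrast and does not carry over to an interaction. For a 10% relative effect at assumed control rates of 50–80% it is 12–37% or 19–63%, depending on whether 1,200 covers both periods or each, before clustering lowers it further.

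The article also calls its design quasi-experimental and speaks of attributing causality, yet under Evaluation Design Strengths and Weaknesses describes the work as "far from a real experiment or quasi-experiment". These statements conflict.

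**What to change.** 1. State as the main record-review analysis of prescription and BP control a repeated cross-sectional DID: arm, period and arm × period as the effect of interest, with facility random effects. Use a binary-outcome model for prescription and BP control and a linear model for BP level.
2. Replace ANCOVA on patient-level mean change with this model, or with an explicit facility-level analysis that adjusts the after value for the facility's before value. Drop ANCOVA for prescription.
3. Describe exit-survey and provider-survey contrasts as associations, because no pre-intervention round is described for them.
4. Reconcile the quasi-experimental and causal wording with the statement in the strengths and weaknesses section.
5. Say whether 1,200 covers both periods or each, and restate power for the interaction, allowing for clustering.

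**Cost.** No new kind of data is needed, since the before-period records are already part of the review. The interval is wider, by about 1.4 to 2 times in the example above, and the 90% power claim cannot stay as written. The DID removes only a fixed gap. It assumes that the regions would otherwise have moved in parallel, which two time points cannot test.
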